## Background

Tobacco use is the single most preventable morbidity and mortality [1]. Though progress has been made in reducing the prevalence of tobacco consumption in the general population [2], high prevalence (75.2% to 85.1%) remains in some vulnerable populations, particularly among people with substance use disorders (SUDs) [3]. Tobacco is responsible for 53% of the deaths in this group, reducing their life expectancy up to 25 years compared to the general population [4].

Smokers with SUDs take up smoking at an early age, consume more cigarettes per day (CPD), and frequently use different tobacco products [3], resulting in increased nicotine dependence [5] and a two to five times lower likelihood of cessation [6]. In SUD treatment settings, tobacco use has been historically considered a minor problem compared to other substances. Smoking was even once considered therapeutic in preventing substance use relapse [7]. People in treatment for SUDs have shown interest in quitting smoking [8] and make more serious attempts (abstinence  ≥ 24 h) when they are offered both psychological and pharmacological assistance [9].

Approximately 81,000 people annually are admitted to specialized treatment centers in Spain for outpatient treatment for SUDs [10]. Alcohol is responsible for four out of 10 admissions, and cannabis for two out of 10. Data from the Spanish Drug Observatory indicate that 44.7% of people admitted to outpatient treatment for alcohol and 83.3% admitted for cannabis use disorder have used tobacco in the previous 30 days [11]. However, only 44% of the SUD Programs in Catalonia (Spain) provide tobacco cessation treatment as part of their portfolios [12].

Given the high concomitant use of tobacco in patients in SUD treatment, its consequences to physical and mental health, and the low deployment of interventions in Spain, there is an urgent need to study which factors promote the introduction of smoking cessation in these programs.

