Exploration of the barriers and facilitators to abstinence and understanding what elements affect the psychiatric symptomatology and the main drug use are relevant to patients in SUD treatment. Acquiring such information will allow the scientific community to design personalized approaches to promote cessation [27, 28] within this vulnerable group. Previous studies associated smoking cessation in this population with sociodemographic variables (i.e., low education level, low socioeconomic status) [29] and other components, such as motivation to quit smoking, self-efficacy, previous experience with quitting smoking [30], expected withdrawal symptoms [31], and assessment of the services received [9]. Proactively identifying positive predictors of change among smokers in this population may help promote smoking cessation; the most frequently reported predictors are a high level of motivation, having had previous quit attempts, and reducing the number of CPD [13, 14].

Barriers to addressing tobacco use during addiction treatment have also been identified among clinicians. The main barriers are lack of knowledge and training, the preconception that quitting smoking simultaneously while being treated for use of other drugs may compromise abstinence, and clinicians’ smoking status [20].

The high number of SUD treatment admissions for alcohol and/or cannabis use, the high prevalence of tobacco use, and the limited number of interventions aimed at promoting smoking cessation in this group prompts research to facilitate new and better interventions in these settings. We designed the ACT-ATAC (“*Abandono del Consumo de Tabaco durante la Atención y el Tratamiento para Alcohol y/o Cánnabis*” [Tobacco cessation among smokers under alcohol and/or cannabis treatment]) study, which aims to:

(1) Explore clinicians' perceptions of the barriers and facilitators (individual and contextual) that influence the implementation of smoking cessation interventions, and the appropriateness of simultaneous or sequential interventions aimed at this group.

(2) Describe changes in tobacco use, motivation to quit, and the barriers/facilitators to quit at the start of treatment and after 12 months of follow-up.

(3) Identify the individual and contextual predictors associated with successful smoking cessation among persons treated for alcohol and/or cannabis use disorder in SUD programs in Barcelona.

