### Cohort of smokers

#### Participants

Inclusion criteria are (1) being a tobacco user (at least one cigarette per week), (2) initiating treatment for alcohol and/or cannabis in one of the SUD participating program, (3) age  ≥ 18 years, (4) under follow-up by participating clinicians, and (5) providing consent. Exclusion criteria are (1) inability to guarantee a 12-month follow-up (due to anticipated mobility problems, etc.) and (2) severe cognitive impairment and/or other communication problems (i.e., not speaking Spanish or Catalan).

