#### Recruitment process and fieldwork

Clinicians working in the participating centers determine whether their patients meet the inclusion criteria described above and invite those patients to be part of the study. Those who accept to participate and complete informed consent procedures are registered using computer software designed for the ACT-ATAC project, including personal identifiers (i.e., name, surname), psychiatric diagnoses, comorbidities, and location data (contact telephone numbers, responsible clinician, clinician's telephone number, etc.). To facilitate the recruitment process, a protocol has been created in the software. After the participant’s data is introduced into the software, he/she is contacted in the first 48–72 h by a research nurse who conducts an extensive interview (see below). The study nurse is independent to any SUD participating center and was recruited exclusively to conduct this interviews. The study procedures are aimed at following up on the tobacco consumption of patients and other variables. The research nurse also informs the patient when he/she will be contacted for follow-up interviews by telephone (at 7 days and 3, 6, and 12 months; Fig. 2).

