### Cohort of clinicians

#### Participants

Clinicians from the province of Barcelona who agree to participate in the study must meet the following inclusion criteria: (1) to be a clinician (psychologist, psychiatric, nurse, social worker, etc.) in one of the public SUD programs in the province of Barcelona, and (2) that does the initial assessment and follow-up of persons with alcohol and/or cannabis abuse disorders, and (3) provides consent. The exclusion criterion is an inability to guarantee a 12-month follow-up (due to anticipated moves, etc.). We expected to include between 20 and 30 clinicians, and 22 clinicians are currently collaborating in the study from 10 different SUD centers.

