#### Variables

The primary dependent variable is self-reported smoking knowledge, attitude, and practice (S-KAP) [48] during the clinician’s work in the SUD program, monitored at baseline of their participation, one week after, and every three months during their participation in the study.

Independent variables are tobacco consumption (never user, former user, and current user), sociodemographic data (sex, age, education level, profession), and professional experience (years treating drug abuse population, years working in the same program). In the case of being a tobacco user, we ask about the tobacco product consumed (i.e., cigarettes, roll-your-own tobacco, combination of both, cigars, e-cigarettes, iQOS); smoking history, including age when starting smoking, maximum abstinence time, previous quitting attempts, and resources used (i.e., none, self-help, professional support, pharmacological treatment, etc.); motivation to quit smoking, measured by a Likert scale from 0 to 10; and willingness to quit smoking, assessed by a 4-item questionnaire according to Prochaska and DiClemente’s model, classifying smokers into five stages of change [36].

Clinicians receive the KAP questionnaire [48] every three months to report data on the approach taken in the care of the smoker (ask, advise, assist).

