## Statistical analysis

After finishing the recruitment and follow-up, abstinence and quit attempt incidence rates will be calculated at baseline and at 3, 6, and 12 months according to whether participants have received any type of smoking cessation intervention. We will also calculate the corresponding risk ratios with 95% confidence intervals (CIs) for quitting and quit attempts.

We will assess the association between receiving smoking cessation support and the two primary outcomes (abstinence and quit attempts) using a Poisson regression model with robust variance for several independent variables (the substance of treatment, sex, types of cessation support [e.g., tobacco-related counselling and medication, etc.]), resulting in RRs with their 95% CIs as their estimators. For analysis, we will use SPSS for Windows version 21 with significance set at p  < 0.05.

We will also conduct exploratory factor analysis for testing the psychometric properties of the S-KAS and S-KAP scales.

S3 (months 40–44): Phenomenological study with discussion groups directed towards patients (will be conducted between December 2022 and June 2023).

This qualitative phenomenological study with discussion groups will use a semi-structured script to answer aim 4.

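### The named Poisson model specifies no clinician or centre clustering, so intervals for contextual predictors are likely too narrow, and those for cessation support possibly so

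*Protocol article*

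**What the plan says.** Protocol article, Statistical analysis: the stated task is "We will assess the association between receiving smoking cessation support and the two primary outcomes (abstinence and quit attempts"). The method named for it is set out as "using a Poisson regression model with robust variance". The independent variables listed are the substance treated, sex and type of support. Risk ratios with 95% confidence intervals are the estimators, with significance at p < 0.05. No clinician or centre term, random effect or cluster unit appears.

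The design described elsewhere in the article is nested:

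- Cohort of smokers, Participants: an inclusion criterion is "4) under follow-up by participating clinicians".
- Recruitment process and fieldwork: "Clinicians working in the participating centers determine whether their patients meet the inclusion criteria described above", and then invite them. The software stores each patient's responsible clinician.
- Cohort of clinicians, Participants: "22 clinicians are currently collaborating in the study from 10 different SUD centers".
- Cohort of clinicians, Variables: the same clinicians complete a questionnaire every three months "to report data on the approach taken in the care of the smoker (ask, advise, assist"). Their own smoking status, profession and experience are recorded as well.
- Background, aim 3: "Identify the individual and contextual predictors associated with successful smoking cessation".

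**The concern.** With a binary outcome, the usual reason for a robust variance in a Poisson model is that the Poisson variance is wrong for 0/1 data. The sandwich estimator repairs that. It allows for correlation between patients of the same clinician or centre only if that unit is declared as the cluster, and none is declared here.

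Correlation is plausible because the same few clinicians select the patients, treat them and give the cessation care. It matters most for predictors with one value per clinician or centre, such as a clinician's smoking status or whether a centre offers cessation treatment. For these the effective sample size is closer to 22 or 10 than to the number of patients. Aim 3 asks about such predictors, and the article says its results should inform healthcare planning. A false-positive rate well above the stated 5% would then bear on the study's main use.

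**Working it through.** **The plan's own figures.** The article gives no ICC and no design effect. Its required size of 366 (Sampling method) can be approached without one: 7% against 14% (the stated risk ratio of 2.0), two-sided 5%, 80% power, arcsine formula gives 293, and 293/0.80 = 366.25. That is a number per group, which is a separate matter. Here it shows only that the figure can be reached with no allowance for clustering.

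**Inputs.** 22 clinicians and 10 centres (Cohort of clinicians, Participants). Target 200 to 250 patients (end of the section on fieldwork and COVID-19 strategies). Losses 20% (Sampling method). Analysed: 200 × 0.80 = 160 to 250 × 0.80 = 200. Assumed: ICC 0.02 to 0.10 and equal cluster sizes.

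**Predictor constant within the cluster.** With m patients per cluster, design effect DE = 1 + (m − 1) × ICC. The standard error is understated by a factor √DE. True type I error = 2 × [1 − Φ(1.96/√DE)]. At ICC = 0, DE = 1 and the formula returns 5%.

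- Smallest case, clinician: m = 160/22 = 7.27; DE = 1 + 6.27 × 0.02 = 1.13; √DE = 1.06; type I error 6.5%.
- Largest case, centre: m = 200/10 = 20; DE = 1 + 19 × 0.10 = 2.90; √DE = 1.70; type I error 25.0%.

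Each cell gives DE, √DE and true type I error:

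| Constant within | Analysed | m | ICC 0.02 | ICC 0.05 | ICC 0.10 |
|---|---|---|---|---|---|
| Clinician (22) | 160 | 7.3 | 1.13, 1.06, 6.5% | 1.31, 1.15, 8.7% | 1.63, 1.28, 12.4% |
| Clinician (22) | 200 | 9.1 | 1.16, 1.08, 6.9% | 1.40, 1.19, 9.8% | 1.81, 1.35, 14.5% |
| Centre (10) | 160 | 16 | 1.30, 1.14, 8.6% | 1.75, 1.32, 13.8% | 2.50, 1.58, 21.5% |
| Centre (10) | 200 | 20 | 1.38, 1.17, 9.5% | 1.95, 1.40, 16.0% | 2.90, 1.70, 25.0% |

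Simulation with 10% abstinence, 200 or 250 patients and the same ICC range agrees broadly: 5.5 to 16.6% with 22 clusters and 7.3 to 25.3% with 10.

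**Support, which can vary within a cluster.** Simulated type I error of the nominal 5% test under the null, ICC 0.02 to 0.10. The 10% abstinence is the rate expected in Sampling method; the 28% is the rate quoted in the Background for concurrent interventions.

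| How support is distributed | Abstinence | Type I error |
|---|---|---|
| Varies freely within clusters | 10% | 3.5–4.7% |
| Partly clustered (exposure ICC 0.2) | 10% | 3.9–8.5% |
| 60% vs 35% by centre (10 × 20 patients) | 10% | 3.7–4.5% |
| 60% vs 35% by centre (10 × 20 patients) | 28% | 5.0–5.6% |
| 80% in 4 centres, 20% in 6 (10 × 20) | 10% | 4.9–10.0% |
| 80% in 4 centres, 20% in 6 (10 × 20) | 28% | 5.9–12.5% |
| 80% vs 20% by clinician (22 × 9) | 28% | 5.2–8.1% |

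The 80/20 pattern is strong clustering. Mean support is 0.4 × 0.8 + 0.6 × 0.2 = 0.44; the between-centre variance is 0.4 × 0.6 × 0.6² = 0.0864; the total is 0.44 × 0.56 = 0.2464; the exposure ICC is 0.0864/0.2464 = 0.35.

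**Which remedy works.** For a centre-level predictor with centre-level correlation (ICC 0.02 to 0.10), clustering on clinician with a t reference on 21 df still gave about 7 to 14%. Plain cluster-robust variance on 10 centres gave 7 to 12%. Centre-clustered variance with a small-sample t reference on 10 − 2 = 8 df gave about 6 to 7%.

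**The case against.** The article never says that patients are treated as independent; that is inferred from silence. A Poisson model with clinician-clustered variance would also fit its wording, and an article may leave the cluster unit to a fuller plan that is not shown. This stands as a limit on the claim: one cannot say that the investigators have chosen independence. It does not remove the point. The article commits to a model and a variance estimator, lists the covariates, and states an aim about contextual predictors that this specification does not serve.

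A reader might also infer that every interval will be too narrow, including the one for support. The documents do not support that. Nothing in them shows how far support differs between the ten centres. The Background says that "only 44% of the SUD Programs in Catalonia (Spain) provide tobacco cessation treatment as part of their portfolios", but that describes all Catalan programmes, not the participating ones, and concerns treatment on offer. The measured support also includes advice and educational material, which a clinician can give to one patient and not another. Where support varies freely within clusters, the simulations show no inflation. Sex and substance treated can also vary within a clinician.

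The largest figures concern centre-constant predictors, and the covariates listed in Statistical analysis include none. That is true, but no other quantitative model is described for aim 3. Finally, all sizes rest on an assumed ICC. At 0.01, with 160 to 200 analysed, type I error is only 5.7 to 5.9% (clinician) and 6.8 to 7.2% (centre).

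**Conclusion.** The point holds in conditional form. Applied as written, the model is likely to give intervals that are too narrow for clinician- and centre-level predictors. At an assumed ICC of 0.02 to 0.10, equal cluster sizes and 160 to 200 patients analysed, those intervals should be 6 to 35% wider for clinician-constant predictors and 14 to 70% wider for centre-constant ones. The corresponding type I errors are about 6.5 to 14.5% and about 8 to 25%. For receipt of support the result is open: from no inflation to a type I error of about 13%, the upper end needing both a strong split between centres and an ICC of 0.10. Confidence is good for contextual predictors and limited for support. The change should be made before analysis, but this does not invalidate the design.

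**What to change.** Keep the log-link Poisson model and the risk ratio. State the cluster unit of the robust variance, at the highest level relevant to each predictor:

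- **Centre-level predictors:** cluster on centre, with a small-sample correction and a t reference whose df come from the 10 centres (8 for a single centre-level predictor). Report these results as exploratory. Clustering on clinician is not enough here.
- **Clinician-level predictors and receipt of support:** cluster at least on the responsible clinician. Where the predictor varies within centres, add a sensitivity analysis with centre-clustered variance or centre fixed effects.
- **Reporting:** give the estimated ICC and the number of patients per clinician and centre, so that readers can see how much clustering there was.

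No new data are needed, since the responsible clinician is already recorded, and the analysis comes after follow-up ends. The costs are wider intervals and few degrees of freedom for centre-level predictors. The documents do not show whether the named software, SPSS 21, offers the small-sample correction; this should be checked, and another package named if it does not.

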#### Sampling method

The incidence of unassisted smoking cessation is seven ex-smokers per 100 patient-years [33]. We estimate that, among this sample, being in contact with the health system may increase this rate to 10 ex-smokers per 100 patient-years (i.e., a relative risk [RR] of quitting smoking of 2.0). Therefore, to detect this RR assuming an alpha error of 5%, a beta error  < 20%, and losses of 20%, we require 366 participants. The sample size was calculated using the GRANMO program [34]. This sample size is achievable in one year as the 48 centers in the province of Barcelona treat approximately 5000 new cases for alcohol and 1500 new cases for cannabis yearly (target population: 6,500 participants) [12]. On average, the 10–12 selected study centers should treat approximately 1,625 people/year. Smokers in treatment for alcohol and/or cannabis use are being recruited consecutively for one year.

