**Fig. 3 Fig3:**
[figure not shown]
Clinician’s mug with the inclusion and exclusion criteria

Moreover, to improve participants’ fidelity in the follow-up study, halfway through the study, we started offering 20 euros gift cards to those who answer all of the phone calls during the 12-month follow-up. At the time of submitting this manuscript, 98 patients have been recruited. Thus, we will continue the study until we recruit at least 200 to 250 participants (expected by the end of 2022).

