**Primary outcome**								
Breathed CO concentration	X		X	X	X	X	X	X

Independent variables include sociodemographic data (sex, age, employment status and occupation, and education level), self-perceived state of health addressed by the question “How would you say your general health is?”, measures of mental and physical health according to the DSM-V [45], quality of life according to the General Health Questionnaire (GHQ-12) [46], and level of previous smoking cessation treatment received using questions about standard interventions included in the Smoking Cessation Guidelines (i.e., advice, reduction recommendation, educational material, cognitive-behavioral treatment, pharmacological treatment, nothing) [47].

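### With about 16 to 20 quitters expected, the robust Poisson test can declare a rarely received type of cessation support significant only because none of its recipients quit

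*Protocol article*

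**What the plan says.** The Statistical analysis section models two outcomes, abstinence and quit attempts, by Poisson regression with robust variance "for several independent variables (the substance of treatment, sex, types of cessation support [e.g., tobacco-related counselling and medication, etc". It promises RRs with 95% CIs and a 0.05 significance level, using SPSS 21. Estimator, covariates and decision rule are therefore all stated. The paragraph before it compares rates by whether any cessation intervention was received, which is a two-group split.

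Kinds of support are itemised among the independent variables of the smoker cohort: "i.e., advice, reduction recommendation, educational material, cognitive-behavioral treatment, pharmacological treatment, nothing". The Statistical analysis section does not say how these items are grouped, or whether they enter one model or several.

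The event count follows from two other places. The Sampling method section expects that "being in contact with the health system may increase this rate to 10 ex-smokers per 100 patient-years" and adds "and losses of 20%, we require 366 participants". The section on fieldwork during the pandemic then lowers the target: "we will continue the study until we recruit at least 200 to 250 participants". No section states what share of participants receives each type of support.

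**The concern.** Low power would be the ordinary worry with so few quitters, but it only widens intervals. The problem here is different: when no recipient of a support type quits, the stated test returns a falsely narrow interval and a vanishing p-value, so the 5% level fails.

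The Discussion says the results should inform future programmes of the Spanish healthcare system. A rarely given form of support could be reported as strongly associated with not quitting, simply because few people received it.

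**Working it through.** **1. The plan's own figure.** Take 7% against 14% ("a relative risk [RR] of quitting smoking of 2.0" applied to 7 per 100), 80% power, and a two-sided 5% level (sidedness is not stated). The arcsine formula gives h = 2·asin√0.14 − 2·asin√0.07 = 0.7670 − 0.5355 = 0.2315. Then n = 2(1.960 + 0.842)²/h² ≈ 293, and 293/0.8 ≈ 366. So 366 reproduces, but as a number per group. The stated rates, 10 and 7, give a ratio of 1.43 rather than 2.0. That is a separate matter; here it only means that expected abstinence could be read as 10% or 14%, and both are carried below.

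**2. Expected quitters.** Over 12 months, 10 per 100 patient-years is about 10%.
- 200 × 0.8 × 0.10 = 16 (160 analysed)
- 250 × 0.8 × 0.10 = 20 (200 analysed)
- Range: 11-14 at 7%; 22-28 at 14%; 45-56 at 28%; about 29 if 366 were enrolled at 10%.

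**3. Chance that a type has no quitter.** This is (1 − p)^n for n recipients. At p = 0.10:

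| Assumed uptake | 160 analysed | 200 analysed |
|---|---|---|
| 5% | 0.9^8 = 43% | 0.9^10 = 35% |
| 10% | 0.9^16 = 19% | 0.9^20 = 12% |
| 15% | 0.9^24 = 8% | 0.9^30 = 4% |
| 20% | 0.9^32 = 3% | 0.9^40 = 1.5% |

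**4. What the estimator returns then.** Take one binary support type with n1 recipients and no quitters among them, and e0 quitters among n0 others. The log RR runs to minus infinity. In the sandwich variance each recipient's residual shrinks in step with the fitted mean, so that arm contributes n1·μ²/(n1·μ)² = 1/n1. The other arm contributes (1 − e0/n0)/e0.
- 160 analysed, 0/8 against 16/152: SE = √(1/8 + 0.8947/16) = √0.1809 = 0.425. The fit gave log RR −19.7, robust SE 0.43 and p effectively 0. The model-based p was 0.999 and Fisher's p 1.0.
- 200 analysed, 0/20 against 20/180: SE = √(1/20 + 0.8889/20) = √0.0944 = 0.307. Robust p was effectively 0; Fisher's p was 0.23.

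Stopping the first fit after five iterations still gave p below 1e-40, so the result does not depend on the convergence limit.

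**5. False-positive rate under no association.** Null simulations used 10% abstinence, the HC0 sandwich and a Wald test at 5%. They had 2,000 or 4,000 runs per scenario, with sex, substance and two or five support types as covariates. Ranges span the separate simulations.

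| Assumed uptake | 160 analysed | 200 analysed |
|---|---|---|
| 5% | 49-50% | 41-43% |
| 10% | 24-26% | 17-19% |
| 15% | 14% | 8% |
| 20% | 7-8% | 5-6% |

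Virtually every zero-quitter type (at least 99.9%) was declared significant. In the runs that split the rate, false positives from other samples added only 3 to 6 percentage points, so the excess over 5% comes from the zero cells. Fisher's exact test rejected in 2-4% of null samples.

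**6. Sensitivity.** At 10% uptake:
- 14% abstinence: about 16% (160 analysed) and 10% (200 analysed).
- 366 enrolled (293 analysed), 10% abstinence: about 9%.
- 28% abstinence, the rate the Background cites for concurrent interventions: 5-7%.

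At 28% abstinence and 5% uptake, a zero cell still has probability 0.72^8 = 7% or 0.72^10 = 4%.

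A single any-versus-none variable, with 44% assumed to be supported, gave 4% at both sizes.

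**The case against.** The strongest objection is that the decisive input, uptake by type, is nowhere in the documents. With every type at 20% uptake or more the error rate is 5-8% and there is little to correct. This stands, and it makes the point conditional. A reader might infer that the trial's error rate is about 25%; the documents do not support that.

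A reader might also infer that the fault is too many coefficients: five types, sex and three substance groups make 8, or 2 to 2.5 quitters each. That model is one reading of an open-ended example naming only counselling and medication, and the itemised list belongs to a variable on previous treatment received. The count is not the driver either, since two-type and five-type models give the same rates at the same uptake.

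The outcome is 7-day abstinence, which may be more frequent than the ex-smoker incidence of 10 per 100, and 200 to 250 is a minimum. Both are fair. At 28% abstinence the problem nearly vanishes for uptake of 10% or more.

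Handling of sparse categories is often left to an analysis plan, and its absence here would be no finding. What is criticised is the test that the article does state, which is invalid in this situation.

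Finally, an RR near 1e-9 beside a count of zero is easy to spot, and SPSS 21, in which these fits were not run, may print a warning. That lowers the chance of misreporting, but the stated p < 0.05 rule does not deal with it.

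**Conclusion.** The concern holds in conditional form. At 16 to 20 expected quitters, the stated robust Wald test is unreliable for any support type received by roughly 15% of participants or fewer. For such a type the false-positive rate runs from about 8-14% at 15% uptake to 40-50% at 5% uptake, against the stated 5%. At 20% uptake it is 5-8%.

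This rests on 10% abstinence, 20% losses, enrolment of 200 to 250, and assumed uptake. The lowered enrolment makes it worse: at 10% uptake the rate is about 9% with 366 enrolled, against 17-26% now.

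Two wider readings are not supported. One is that quit attempts are affected in the same way; the documents give no rate for that outcome, so it cannot be shown. The other is that the artefact would defeat aim 3. That aim concerns individual and contextual predictors of cessation and does not name types of support, although the analysis section tests them.

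**What to change.** In the Statistical analysis section, keep the robust Poisson model and make its main abstinence version any-versus-none support with substance of treatment and sex. The section's first paragraph already uses that split. It is safe as long as neither group is very small.

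For individual types of support, report quitters over recipients. Where a type has no or very few quitters, replace the robust Wald p-value and CI with an exact, score or Firth penalised-likelihood interval, or merge the type with a related one. State the rule before the outcome data are examined. A reader might infer that all type-specific adjusted RRs must go; they need not, because types with enough quitters can stay in the model.

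The cost is slightly more analysis work, possibly software other than SPSS 21, and no usable adjusted RR for the rarest types. Data collection does not change.
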